### Statistical considerations

#### Required number of patients

The phase II is based on a two-step optimum Simon design [52] for the experimental arm, with the same number of patient in the control arm. The control arm allows checking that patients included are comparable to those included in previous studies that led to build study hypotheses, and to expand this study in a Phase III study by using a phase II-III design, depending on the study results.

The hypotheses are the following:18-months hepatic RFS rate with the control treatment of 30%18-months hepatic RFS rate with the experimental treatment of 50%A minimum follow-up time of 18 months for patient alive without recurrence.

With this hypothesis and to have a 95% power (beta risk = 5%) and a one-sided alpha risk of 10%, a total of 108 patients will have to be randomized. Since 5% of patients will be non-evaluable, a total of 114 patients will be included. The rate of non-evaluable patient will be monitored and if necessary an increase in sample size will be proposed. After the inclusion of the first 30 evaluable patients, an analysis on safety and feasibility after 6-month follow-up will be performed and reported to the independent data monitoring committee (IDMC).

An interim efficacy analysis in both arms will be performed after the inclusion of the first 30 evaluable patients with a minimum of 18-month follow-up in the experimental arm as planned by the Simon design. This analysis will be reported to the IDMC. Among the first 30 evaluable patients in the experimental arm,If 7 on the experimental arm or fewer patients were free of hepatic recurrence at 18 months, the Phase II will be stopped because of poor efficacy and the trial will be stopped.If 8 or more patients on the experimental arm were free of hepatic recurrence at 18 months, the Phase II will continue and the Phase III (or its activation) will be continued.

After evaluation of 18-month RFS in 54 evaluable patients,if 20 or less patients out of the 54 of the experimental arm were free of hepatic recurrence, the trial will stop because of poor efficacy.Otherwise, the conclusion will be that the 18-month RFS is good enough to continue or open to accrual the Phase III study.

For the Phase III, the primary endpoint will be 3-year recurrence-free survival (RFS) rate. Patients randomized in the Phase II will be included in the Phase III. The hypotheses are the following:3-year RFS rate with the control treatment of 15%3-year RFS rate with the experimental treatment of 30%, (HR 0.63)

With this hypothesis (α- risk, 5% (two-tailed); β- risk, 20%), the corresponding number of patients is 204 patients (152 events). With an increase of 7–8% (ineligible patients etc.…), the total number of patient is: 220 (164 events), i.e. 110 patients/arm, including 106 additional patients in the Phase III.

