## Methods/ design

This study is designed as a multicenter, randomized phase II/III trial. The first step is a non-comparative randomized phase II trial. Its main objective study is to assess the efficacy of HAI oxaliplatin plus systemic fluoropyrimidine (LV5FU2 regimen) after curative-intent surgery (resection and/or thermal ablation) of at least 4 CRLM. Depending on the results, this randomized phase II study will be expanded into a phase III study to demonstrate the superiority of adjuvant HAI chemotherapy compared to systemic chemotherapy. The phase III will include the patients of the phase II and an additional group of patients to reach the total sample size needed for the phase III. If confirmed, this will have a clinically relevant impact on patient survival and an impact on public health because of the frequency of CRLM.

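### Cheap improvement: apply the futility stop as soon as the failure count has settled it (23 of 30, then 34 of 54), without waiting for 18 months of follow-up on every counted patient

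*Protocol article*

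**What the plan says.** All of this is in the protocol article, section Required number of patients, unless noted.

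- **Timing of the first efficacy look.** "An interim efficacy analysis in both arms will be performed after the inclusion of the first 30 evaluable patients with a minimum of 18-month". The 18 months are the observation time required of each of these experimental patients.
- **Stage-1 rule.** With 7 or fewer of these 30 free of hepatic recurrence at 18 months, the trial stops. With 8 or more, "the Phase II will continue and the Phase III (or its activation) will be continued".
- **Stage-2 rule.** With 20 or fewer of 54 free, the trial stops. Otherwise phase III is continued or opened.
- **Design inputs.** For control, "18-months hepatic RFS rate with the control treatment of 30" (per cent). For the experimental arm, "18-months hepatic RFS rate with the experimental treatment of 50" (per cent). For the error rates, "95% power (beta risk = 5%) and a one-sided alpha risk of 10" (per cent).
- **Size before inflation.** "a total of 108 patients will have to be randomized".
- **Size after inflation.** "Since 5% of patients will be non-evaluable, a total of 114 patients will be included".
- **Other monitoring.** An earlier report to the data monitoring committee, at 6 months of follow-up, covers safety and feasibility only.
- **Link to phase III** (Methods/ design): "Depending on the results, this randomized phase II study will be expanded into a phase III study".

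The article gives no accrual rate, no accrual hold while the 18 months run, and no provision to act before the look if the boundary has already been crossed.

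**The concern.** A boundary on a count can be settled before the last patient completes follow-up. Once 23 of the 30 have failed, at most 7 can be free at 18 months, whatever happens to the rest. From then on, waiting cannot change the stop/go decision. If accrual continues, as the text leaves possible, patients go on being randomized in a trial that has met its own stopping rule, half of them to an arm that needs an implanted hepatic arterial catheter. The same holds at the final phase II look from the 34th failure among 54. What is at stake is a number of months and patients, not the validity of the design.

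**Working it through.** **1. The plan's own figures.** Exact binomial for 7/30 then 20/54:

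- P(stop at stage 1) = P(X ≤ 7 | n = 30) = 0.281 at p = 0.30, 0.761 at p = 0.20 and 0.0026 at p = 0.50.
- P(declare promising) = Σ over x ≥ 8 of P(X₁ = x)·P(X₂ > 20 − x), with X₁ ~ Bin(30, p) and X₂ ~ Bin(24, p). This is 0.102 at p = 0.30 (type I error, slightly above the stated 10%) and 0.961 at p = 0.50 (power, stated as 95%).
- Inflation: 108/0.95 = 113.7, so 114.

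**2. When the boundary is settled.** Stage 1: 30 − 7 = 23 failures. Stage 2: 54 − 20 = 34 failures. At least 23 failures among the 30 is the same event as at most 7 free, so the probabilities in step 1 are unchanged if the trial stops at the 23rd failure.

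**3. When the planned look falls.** With 1:1 allocation, 30 experimental patients means about 60 randomized, or 60/0.95 = 63.2 if 5% are non-evaluable. For accrual *a* per month over both arms (an assumption), the look is at month 60/*a* + 18, with 60 + 18*a* patients randomized if accrual goes on. All 114 are in by then if *a* ≥ (114 − 60)/18 = 3.0, or (114 − 63.2)/18 = 2.8 with non-evaluables.

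**4. Gain from acting at the 23rd failure.** Simulation; exponential failure times, failures seen at the 3-monthly visits, no accrual hold, enrolment capped at 114. Averages are over trials that cross the boundary. The lower end is a true rate of 30%, the upper end 20%.

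| Accrual per month | Planned look (month) | Phase II patients in at the look | Months earlier | Phase II patients spared, both arms |
|---|---|---|---|---|
| 1 | 60/1 + 18 = 78 | 78 | 10-14 | 10-14 |
| 2 | 60/2 + 18 = 48 | 96 | 8-10 | 15-21 |
| 3 | 60/3 + 18 = 38 | 114 | 6.5-9 | 17-23 |
| 4 | 60/4 + 18 = 33 | 114 (full) | 5.5-8 | 8-14 |

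At 4 a month the saving falls because the 114th patient enters at month 114/4 = 28.5, before the look.

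**5. Sensitivity at 3 a month.**

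- Steady accrual, all evaluable: 114 − 94.6 = 19.4 to 114 − 87.7 = 26.3 spared.
- Steady accrual, 5% non-evaluable: 114 − 97.1 = 16.9 to 114 − 90.2 = 23.8.
- As the previous line, with Weibull failure times: shape 0.7 gives 114 − 93.2 = 20.8 to 114 − 85.5 = 28.5; shape 1.4 gives 114 − 100.5 = 13.5 to 114 − 94.4 = 19.6.

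**6. Averaged over all trials at 3 a month.** At p = 0.30: 0.28 × 17 = 4.8 patients, about 2.4 in the experimental arm. At p = 0.20: 0.76 × 23 = 17.5, about 8.7 in the experimental arm.

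**7. Stage 2.** At p = 0.30 a further 1 − 0.102 − 0.281 = 0.617 of trials stop at the final phase II look. Acting at the 34th failure comes about 13.3, 11.1 and 9.7 months earlier at 2, 3 and 4 a month. If phase III accrual is already open, that is about 27, 33 and 39 fewer randomized. Counted within the 114 only, it is under 2 patients at 3 a month and almost none at 4.

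**The case against.** - **A fixed look is the usual way to run a Simon design, and an accrual hold may be in the full protocol.** Both stand. The printed timing is not an error, and the lack of a hold is read from silence in a condensed article. The point is therefore an improvement to a rule that is printed in full, not a defect.
- **A reader might infer that the look comes too late to act, or protects few or none.** The documents do not support this. No accrual rate is given, and 3 a month sits at the break-even. At 2 a month 96-99 of the 114 are in at the look, at 1 a month 78-81. Even at 3 a month the planned stop ends the whole trial and leaves 220 − 117 = 103 to 220 − 114 = 106 patients unrandomized.
- **A reader might also infer that the phase III clause in the stage-1 rule contradicts Methods/ design and should go.** It does not clearly do so. The stopping rules twice allow phase III to be open already, and dependence on the phase II results does not plainly exclude the interim result. Holding phase III until 54 experimental patients reach 18 months could leave a gap of about 18 months. That is a trade-off for the sponsor.
- **Later follow-up still has uses.** This stands in part. It cannot change the count decision, but the look covers both arms, and the control arm is there to check that the patients match the design assumptions. An earlier stop gives that check less follow-up.
- **Failure needs a definition.** This stands. Under Secondary objectives, a non-hepatic first recurrence is censored and death counts as an event, while the rule counts patients free of hepatic recurrence. The running count must use the same definition as the 18-month count.

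**Conclusion.** The point holds as a cheap improvement. The stage-1 stop waits for 18 months of follow-up on all 30 patients although the 23rd failure already decides it. Acting then leaves every decision, the type I error (0.102) and the power (0.961) as they are.

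The size is moderate and conditional. In trials that cross the boundary the stop comes about 5.5 to 14 months earlier across 1 to 4 patients a month and spares roughly 8 to 23 of the 114 phase II patients, half of them experimental; the number is larger if phase III is already accruing. In the 72% of trials that do not cross the stage-1 boundary at a true rate of 30%, stage-1 curtailment changes nothing. The upper ends rest on a true rate of 20%, below the plan's own 30% for control. The stage-2 version spares a material number of patients mainly if accrual is slow or phase III is open.

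The timing figures rest on assumed accrual, failure-time shape and uninterrupted enrolment. The equality of decisions needs only that the 30 (and 54) patients are fixed by order of entry and that counted failures are not later removed.

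**What to change.** Add to Required number of patients that the data monitoring committee is notified, and the printed stop rule applies, as soon as 23 of the first 30 evaluable experimental patients have failed, and likewise at 34 failures among the 54. State that these patients are fixed by order of entry and that failure is defined exactly as in the printed 18-month count. If either boundary is revised, recompute the trigger as the number of patients minus the boundary. Leave the phase III activation clause as it stands.

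Cost: one sentence, a running failure count at the data centre, and less follow-up in both arms at the time of a stop, so a less mature 18-month estimate and a weaker control-arm check. Sample size and error rates do not change.

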#### Statistical analysis plan

The phase II analysis will be conducted on all the patients registered and randomized, in “intention to treat”. A second analysis will be conducted on the “treated” population, determined according to the treatment actually administered (per protocol analysis). The phase III analysis will be performed according to intent-to-treat principle, i.e. on all patients randomized. A minimum follow-up of 18 months for the last enrolled patient will be required.

The results for the primary and secondary endpoints will be presented by arm with a confidence interval at 95% (Rothman for survival data). Compliance data will be reported by number of cycles. The total dose of 5-FU (overall and according to its modalities: (bolus, continuous perfusion) by square meter, as well as the total dose of oxaliplatin (overall and according to its modalities: IA and IV) and the type and dose of target therapy if any will be described. The corresponding dose-intensity will be computed. Information on the treatment of recurrence will be also collected. Safety data will be reported according to their frequency and by system organ class. Analysis per patient (maximum grade) and per cycle will be reported. The proportion of patient with at least one grade 3 or more toxicity will be computed. For overall survival, survival rates at 12 and 24 months and median will be calculated. For hepatic and overall RFS, rates at 12 and 18 months and median will be calculated. Pattern of recurrences will be also described. As the trial is constructed as a phase II, no statistical test will be made.

The analysis on the 3-year RFS, the primary endpoint for the phase III, will be performed once the number requested of events will be reached and a median follow-up of at least 3 years observed. A long-term follow-up analysis with a minimum follow-up of 3 years and a median follow-up of at least 5 years will be also performed. Main endpoint and secondary efficacy endpoint will be compared by logrank test and reported with a hazard ratio and its 95% confidence interval. Data on compliance and safety will be compared by Wilcoxon or Chi^2^ test as appropriate.

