### Treatment schedule

Randomization will be either performed during surgery, or within 6 weeks after surgery using web-based procedure (TenAlea®). Adjuvant chemotherapy must begin within 8 weeks after surgery. Patients will be randomly assigned using minimization procedure in a 1:1 ratio to:Arm A (control arm): adjuvant systemic (i.v.) chemotherapy (FOLFOX) administered every 14 days:Oxaliplatin 85 mg/m^2^ in 2 h IV day (D)1,Folinic acid 400 mg/m^2^ in 2 h IV (concomitantly to oxaliplatin) D1, followed by5FU bolus 400 mg/m^2^ in 5–10 min IV D1 followed by5FU 2400 mg / m^2^ IV in 46 hArm B (experimental arm): adjuvant HAI chemotherapy plus systemic chemotherapy (LV5FU2) administered every 14 days:Oxaliplatin 85 mg/m^2^ in 2 h HAI D1,leucovorin 400 mg/m^2^ in 2 h IV (concomitantly to oxaliplatin) D1, followed by5FU bolus 400 mg/m^2^ in 5–10 min IV D1 followed by5FU 2400 mg / m^2^ IV in 46 h

Randomization will be stratified according to the following factors:Tumor response to preoperative chemotherapy (objective response vs. stable disease)Number of resected CRLM (4–8 vs. > 8)Center

Patients will receive adjuvant chemotherapy (HAI or systemic) for a maximal duration of 6 months and at least 3 months for the postoperative period. The minimal duration of chemotherapy (pre- and postoperative period) will be of 6 months. Before starting adjuvant chemotherapy, CT scan of the abdomen, pelvis and chest and serum tumor markers will be done (within 4 weeks before starting adjuvant chemotherapy). In both arms, continuation of targeted therapy (if any) used in the preoperative treatment will be allowed.

The HAI catheter will be placed before initiating treatment, either surgically or percutaneously by interventional radiology and bound to an implantable port. Angiographic and/or scintigraphic verification of the HAI catheter functionality will be done within 28 days before the start of treatment. HAI chemotherapy should be performed by physicians and nurses familiar with this technique.

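### The phase III log-rank test and hazard ratio do not use the factors on which patients are minimized; using them would be a nearly free gain in efficiency if those factors are prognostic

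*Protocol article*

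**What the plan says.** In the protocol article, Treatment schedule states: "Patients will be randomly assigned using minimization procedure in a 1:1 ratio". It then adds "Randomization will be stratified according to the following factors" and lists three: "Tumor response to preoperative chemotherapy (objective response vs. stable disease"), number of resected metastases in two classes, and center ("Number of resected CRLM (4–8 vs. > 8)Center").

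Required number of patients sets the phase III assumptions as a 3-year RFS of 15% in the control arm and "3-year RFS rate with the experimental treatment of 30%, (HR 0.63"). The size follows: "With this hypothesis (α- risk, 5% (two-tailed); β- risk, 20%), the corresponding number of patients is 204 patients (152 events"). This is then raised to 220 patients and 164 events.

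Statistical analysis plan fixes the phase III comparison: "Main endpoint and secondary efficacy endpoint will be compared by logrank test and reported with a hazard ratio and its 95% confidence interval". No stratified log-rank test, no stratified or adjusted Cox model and no re-randomization test is named there or elsewhere in the article.

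**The concern.** Factors are normally chosen for minimization because they are thought to be prognostic. Once allocation forces the arms to be alike on such factors, part of the chance variation between arms has been removed by design. A plain log-rank test does not know this and still counts that variation. If the factors matter, its variance is therefore too large: the test rejects less often than its nominal 5% under the null and less often than it could under the alternative. The unadjusted hazard ratio also lies closer to 1 than the hazard ratio within strata.

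At stake is efficiency. Phase III aims at only 80% power, so a few points of power from data already held are worth having. It also helps to settle the choice between a stratified and a plain test before the phase III data are seen.

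**Working it through.** **Inputs from the article.** 3-year RFS 15% vs 30%; two-sided alpha 5%; power 80%; 152 events before inflation, 164 after; 220 patients; 1:1 minimization on response, number of metastases and center.

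**Step 1: reproduce the planned events.** Under proportional hazards, HR = ln(0.30)/ln(0.15) = 0.6346, so ln HR = −0.4547. Schoenfeld's formula for 1:1 allocation gives

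D = 4(1.960 + 0.842)²/(ln HR)² = 4 × 7.849/0.2068 ≈ 152.

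This matches the article. It is the formula for an ordinary, unstratified log-rank test, which agrees with reading the stated test as unstratified.

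**Step 2: formula power.** Power = Φ(½√D × 0.4547 − 1.960). At 152 events this is Φ(0.843) = 80.0%; at 164 events it is Φ(0.952) = 82.9%.

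**Step 3: simulate the stated design.** The setup was 220 patients, analysis at 164 events, minimization on two binary factors and center, and 4000 runs per scenario. The following are assumptions, because the article does not give them: 35% of patients in the worse level of each factor, 12 centers, a biased coin of 0.8, no center effect, and a hazard ratio of 1.0 to 2.0 for each factor. The treatment hazard ratio is 0.635 within strata. The Monte Carlo standard error is about 0.35 points for alpha and 0.6 points for power.

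| HR of each factor | Alpha: plain / stratified / adjusted Cox | Power: plain / stratified / adjusted Cox |
|---|---|---|
| 1.0 | 5.1 / 5.4 / 5.3% | 82.3 / 81.9 / 82.2% |
| 1.3 | 4.9 / 5.1 / 5.3% | 81.2 / 81.5 / 82.4% |
| 1.5 | 4.3 / 5.0 / 5.1% | 80.0 / 81.7 / 83.0% |
| 2.0 | 3.6 / 5.4 / 5.4% | 76.1 / 82.1 / 83.3% |

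The mean unadjusted hazard ratio is 0.645 at factor HR 1.5 and 0.664 at 2.0, against about 0.63 adjusted.

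**Step 4: second simulation, also at 164 events (plain / stratified).** Alpha was 4.9/5.1% at factor HR 1, 4.1/4.8% at 1.5 and 3.9/4.7% at 2.0. Power was 82.6/81.4%, 79.4/80.6% and 76.1/81.4%.

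**Step 5: combine.** The power given up by the plain test is:
- factor HR 1.3: 81.5 − 81.2 = 0.3 to 82.4 − 81.2 = 1.2 points;
- factor HR 1.5: 80.6 − 79.4 = 1.2 to 83.0 − 80.0 = 3.0 points;
- factor HR 2.0: 81.4 − 76.1 = 5.3 to 83.3 − 76.1 = 7.2 points.

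If neither factor is prognostic, stratifying costs 82.3 − 81.9 = 0.4 to 82.6 − 81.4 = 1.2 points.

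**Step 6: hold the planned overall effect fixed.** Steps 3 and 4 fix the hazard ratio within strata, so the overall effect shrinks as the factors get stronger. The plan is written in overall rates. With the effect calibrated to 15% vs 30% overall and 164 events, the plain test has about 82–86% power for factor hazard ratios from 1 to 2.

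**The case against.** **The article is silent; it does not choose.** It says log-rank without saying unstratified, and a journal article may leave strata to a full protocol or SAP that is not shown. This limits how firmly one can say that the factors will be ignored. It does not remove the point: the article names the test and the effect measure, its event number matches the unstratified formula, and the proposed change is to that stated method. If the full SAP already stratifies, confirming this closes the matter.

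**The factors may not be strongly prognostic.** This stands. The Background section names four or more metastases as the factor common to the prognostic scores, but every patient here has at least four, and nothing is said about 4–8 vs >8. In the retrospective series of 98 such patients, HAI and R0 margin were the only independent factors for DFS. The covariates tested are not listed and the series is small, so a strong effect is made less likely but not excluded.

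**Three stronger readings are tempting and not supported.**
- A reader might infer that the primary test has a true size below 5%. That holds only if the factors are prognostic; at factor HR 1.0 or 1.3 the simulated size cannot be told from 5%.
- A reader might take 76% as a shortfall against the planned 80%. It comes from fixing the effect within strata; with the planned overall rates the plain test keeps at least 80% (Step 6).
- A reader might call the unadjusted hazard ratio biased. Its movement toward 1 reflects non-collapsibility. The marginal hazard ratio is a legitimate quantity and is the one the sample size was built on.

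**Conclusion.** The mismatch between allocation and stated analysis is real, and its consequence is a possible loss of efficiency, not an error. At a fixed within-stratum hazard ratio of 0.635 the plain test gives up about 0–1 points of power at factor HR 1.3 each, 1–3 at 1.5 and 5–7 at 2.0, with alpha about 4.1–4.3% at 1.5 and 3.6–3.9% at 2.0. If neither factor is prognostic, nothing is lost. The direction is secure if the factors are prognostic. The size rests on factor hazard ratios, prevalences and a number of centers that the article does not give. Any departure from 5% is on the conservative side, so the validity of the phase III test is not in question.

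**What to change.** State in the analysis section that the primary RFS test and the log-rank tests of the secondary efficacy endpoints are stratified by response to preoperative chemotherapy (objective response vs stable disease) and number of resected metastases (4–8 vs >8). Take the hazard ratio and 95% confidence interval from a Cox model stratified or adjusted on the same two factors. Leave center out of the strata, as too sparse, and say so. Keep the unstratified test as a sensitivity analysis. If the full SAP already says this, confirm it.

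The cost is one sentence. Both factors are already recorded for the minimization, and no change to sample size or event number is needed. If neither factor turns out to be prognostic, about 1 point of power is lost.
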